#### Inclusion criteria

Children and adolescents with an indication for hospitalization for the purpose of weight loss - as set by their responsible primary or secondary care physicians - and with a BMI scoring higher than the 97th percentile specific for age and gender will be included
[67]. The age range is set between 9 to 17 years. An indication for inpatient rehabilitation is given if the child suffers from diseases that are relevant or have negative impact on education, training or earning capacity (emotional, social development, personal development), especially for disorders/diseases that could have negative effects on the functioning of the particular age-appropriate levels of activity and social participation in all spheres of life. Medical rehabilitation is part of a long-term management of chronically ill children and adolescents and their families. The goal is an improvement, but at least to prevent deterioration (stabilization) of the health status-quo with regard to the current or future needs in education, training and profession. Requirement for inpatient rehabilitation is that the available outpatient options have been exploited and that a beneficial effect of the disease process can be expected.

#### Exclusion criteria

Children with severe psychiatric comorbidities, linguistic or intellectual limitations (by judgment of the treating physician or therapist), type-1 diabetes, tumors, systemic disorders, or severe cardiovascular diseases will be excluded.

#### Control group

A healthy normal weight reference group of 30 children with the same exclusion criteria will be recruited for potential predictor parameters for which age and gender-specific norm data are missing in the literature. These children will come from the catchment area of the University Hospital Tübingen, Germany.

### Outcomes

#### Primary outcome

The primary outcome measure is the change of the body mass index standard deviation score (BMI-SDS)
[68]. SDS values indicate how many standard deviations an individual’s BMI lays above or below an age and gender matched median of BMI, a deviation of the value about two standard deviations above (+2) corresponds to the 97.7 percentile of the reference group
[69]. Reference data for German children are used
[67]. In order to calculate the BMI, the body weight and body height will be measured upon admission and upon discharge of their inpatient stay using calibrated instruments.

#### Secondary outcomes

Secondary outcomes measures include the changes in body composition and motor performance. Body composition is measured by a lipometer© (Möller Messtechnik, Graz, Austria)
[70-72]. The motor performance is assessed by the Dordel-Koch-Test
[73].

### Appointments

After informed consent, the hospital planning office will receive a screening form with psychophysiological assessments and will include the child into the study, depending on the particular time-slots available for the child. Afterwards, it will integrate four half-day assessments into the individual therapy plan. This procedure avoids time conflicts with other therapies and insures that the investigations are completed within the first week after admission and during the last week prior to discharge.

The children will pass two test sessions upon admission, one in the morning and one in the afternoon, and the same test sessions will be repeated prior to discharge. On both occasions, a series of investigations will be performed which can be grouped into four clusters: 1) demographic, sociometric and psychometric data 2) objective and subjective parameters of body condition, 3) autonomic nervous system regulated functions and 4) objective and subjective parameters for eating behavior (see below).

### Psychophysiological investigations

Within and across the discussed clusters, the number of measures chosen is based on theoretical (previous data available) as well as pragmatic reasons (feasibility, availability). For logistic reasons, the investigations are split into two groups, one of which is conducted during a morning session (9.00 h to 12.00 h), while the other one is conducted on a separate day in the afternoon (14.00 h to 16.00 h) (see Table 
1). In addition, clinical data from the medical charts will be collected for the analysis. A list of all used questionnaires (of all clusters) is provided in Tables 
2 (children) and
3 (parents).

**Table 1 T1:** Measurement protocol

**Time a.m.**	**First session**	**Approximate duration**	**Time p.m.**	**Second session**	**Approximate duration**
**8:50**	**Welcome/general questions**	**5-10 min**	**14:30**	**Welcome**	**5-10 min**
	**Anthropometry**	**5-10 min**		**Media consumption questionnaire**	**5-10 min**
	**Sleep Self Report (SSR)/Pediatric Daytime Sleepiness Scale (PDSS)**	**7-10 min**		**Interoception test**	**5 min**
	**Taste test**	**5-10 min**		**ECG/EGG/SCL Baseline**	**20 min**
	**Inventory for recording the Quality of life in Children and Adolescents (ILK)**	**3-5 min**			
	**Smell test**	**15-20 min**		**Stress test**	**5 min**
	**Inventory of Eating and Weight problems Inventory for Children (EWI-C/IEG-K)**	**15-20 min**		**Post stress test**	**20 min**
	**Dordel- Koch test**	**15-20 min**			
	**Somatization Inventory for Children and Adolescents (SI-KJ)/State-Trait Anxiety Inventory (STAI-C)**	**5-10 min**		**Water load test**	**2-5 min**
				**Post water load**	**20 min**
	**Cognitive ability to discriminate volumes of food and liquids**	**15-20 min**		**Eating behavior test with snacks**	**20 min**
	**Depression Inventory for Children and Adolescents (DI-KJ)**	**10-15 min**			
	**Body image**	**10-15 min**		**Stress and Stress Coping Questionnaire for Children and Adolescents (SSKJ-J)**	**15-20 min**
	**Self-esteem scale by Rosenberg**	**2-5 min**			
**11:30**	**Farewell**		**17:00**	**Farewell**	

**Table 2 T2:** Questionnaires for children

**Questionnaires**	**Short description**
Sleep Self Report (SSR) [74,75]	28 items; three thematic areas; three answer options ranging from “common” to “uncommon”
Pediatric Daytime Sleepiness Scale (PDSS) [76]	32 items; six thematic areas; five Answer options ranging from “always” to “never”
Inventory for recording the Quality of life in Children and Adolescents (ILK) version for children [77]	10 items; seven thematic areas; five answer options ranging from “very good” to “very bad”
Inventory of Eating and Weight problems Inventory for Children (EWI-C/IEG-K) [78]	60 items; ten subscales; four answer options ranging from “not true at all” to “totally agree”
Somatization Inventory for Children and Adolescents (SI-KJ) [79,80]	35 items; list of symptoms; five answer options ranging from “not at all” to “much”
State-Trait Anxiety Inventory (STAI-C) [81,82]	20 items; two scales; three answer options ranging from “almost never” to “often”
Depression Inventory for Children and Adolescents (DI-KJ) [83]	26 items; queries gradations of symptoms; decision between three predefined answer alternative
Stress and Stress Coping Questionnaire for Children and Adolescents (SSJK) [84]	84 items; three subscales; five answer options ranging from “never” to “always”
Revised self-esteem scale by Rosenberg	10 items; total score from 10–40, the higher the score the higher the level of self-esteem; Four answer options ranging from “strongly disagree” to “strongly agree”

**Table 3 T3:** Questionnaires for parents

**Questionnaires**	**Short description**
Pediatrics Sleep Habits Questionnaire (PSQ) [85]	22 items; three subscales; Answer options: Item 1 to 16: “yes“, “no”, “don’t know”; item 17 to 22: four options ranging from “does not apply” to “meets most of time”
Epworth Sleepiness Scale (ESS-E) [86,87]	8 items; total score from 0–24; four answer options ranging from “would never doze” to “dozing high probability”
Children’s Sleep Habits Questionnaire (CSHQ) [88,89]	33 items; eight subscales; three answer options ranging from “common” to “uncommon”
Subjective Strength and Weaknesses (SDQ) [90,91]	25 items; five subscales; three answer options ranging from “does not apply” to “clearly applicable”
Inventory for recording the Quality of life in Children and Adolescents (ILK) version for parents [77]	11 items; nine thematic areas; five answer options ranging from “very good” to “very bad”

#### Cluster 1: Sociometrics and psychometrics

Besides conventional sociodemographic data (family history and status, social status, education etc.) all children will complete the following psychometric questionnaires, usually in validated German translations: a health-related quality-of-life scale (ILK, children and adults)
[77], a depression scale (DIKJ)
[83], a somatization scale in dependence on the International Children’s Somatization Inventory (CSI/SI-KJ)
[79,80], the trait anxiety scale (STAI-C)
[81,82], screenings for emotional and behavioral problems (SDQ)
[90,91], and the self-esteem scale according to Rosenberg
[92].

#### Cluster 2: Physical condition measures

The children will complete the Sleep Self Report (SSR)
[74,75] which records sleep problems, and the Pediatric Daytime Sleepiness Scale (PDSS)
[76]. Parents will fill in the Pediatrics Sleep Habits Questionnaire (PSQ)
[85], a screening tool for sleep behavior, the ESS-E
[86,87] determining daytime sleepiness, and the Children’s Sleep Habits Questionnaire (CSHQ)
[88,89] once at the beginning of the therapy.

The Dordel – Koch test
[73] will be used to capture the basic functions and motor performances of children and adolescents. The test battery consists of lateral jumping back and forth (coordination under time pressure, speed), sit and reach (flexibility of the hips and lower spine), standing long jump (explosive strength of the lower extremity), sit-ups (strength of the abdominal muscles and hip flexors), standing on one leg (coordination with precision tasks), push-ups (strength of the shoulder, chest and arm muscles) and the 6-minute walk distance (aerobic endurance). Additionally, physical fitness will be recorded by a regular bicycle ergometry program supervised by specially trained staff during the regular course of therapy. Body composition will be recorded by a lipometer© (Möller Messtechnik, Graz, Austria) that enables a non-invasive, fast, accurate, and reliable measurement of the thickness of subcutaneous fat
[70-72] including hip and waist circumference. Moreover, the method is evaluated by a data set of 1351 juveniles of which 101 were obese
[93]. In addition, anthropometric measures of various body parts will be collected by tape, calipers, and a scale. Thoracic breadth and depth will be assessed in order to detect the type of physiques according to the “Metric-Index"
[94].

The interoception test according to Schandry
[38] will test the ability of the children to correctly perceive body-internal cardiac signals (heart beat)
[47,95]. During four intervals of 25, 35, 45, and 55 seconds duration, separated by 30 second resting periods, an electrocardiogram (ECG) will be recorded and children shall count their own heartbeats. A start and stop cue signals beginning and end of the counting phases. Participants are not allowed to take their pulse or to attempt any other manipulation that can facilitate the detection of heartbeats. Following the stop signals, children will be asked to report the number of counted heartbeats that will be evaluated against the recorded heart rate. Furthermore, a test for perception of their own body image will be performed by means of estimation of size of their body (total, parts) in relation to various external objects and sensory cues. Standardized tests for chemosensitivity (smell, taste) using validated tools (Burghart Messtechnik GmbH, Wedel, Germany)
[96,97] to measure their respective thresholds, identification and discrimination ability will be conducted.

#### Cluster 3: Autonomic regulation

An electrocardiogram (ECG) will be recorded for off-line analysis of heart-rate variability (HRV) during rest (20 min) and following a mental stress test (counting backwards in steps of 7 from 1000, 300, or 100, depending on the age and intellectual level of the children; 20 min). Afterwards, the children will be asked to rate the perceived stress level on a scale between one (absolutely not stressed) to six (absolutely stressed). The ECG is recorded for inter-beat intervals (IBI) allowing Fast Fourier Transformation of data to estimate heart rate variability (HRV) parameters (high and low frequency (HF, LF)).

At the same time, three surface electrodes placed over the upper abdomen will record myoelectrical activity from the stomach (EGG)
[98] for off-line analysis. At the end of the session, a water loading test
[99,100] will be performed to determine the response of the stomach to an intragastric strain associated with gastric filling: subjects will be asked to drink as much water as possible within 5 minutes until the feeling of fullness is reached. The water load test will be followed by a 20 minutes measurement of the EGG. EGG signals will be analyzed with a Fast Fourier Transformation (FFT) procedure. A frequency of 3 cycles per minute (cpm) is regarded as normal gastric activity and between 4 to 10 cpm as tachygastria. This allows calculating the percentage spectral power from the total range of myoelectric gastric activity and computing the ratio between the percentage of the normogastria and the tachygastria band. This ratio has repeatedly been described as an indicator for disturbed myoelectric gastric activity, for example in patients with gastroparesis
[99], but also in obesity
[46].

Skin conductance will be measured parallel to ECG and EGG by using two separate finger electrodes on the dominant hand. For ECG, EGG and skin conductance measurement, a portable system (3991/3-GPP BioLog, UFI Company, Morrow Bay, CA, USA) will be used. Furthermore, a questionnaire survey of experience of stress and coping in childhood (SSKJ 3–8)
[84] is added to cluster three.

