#### Subjective and objective measures of eating behavior

Smell and taste are often altered in patients with eating disorders and obesity, even in children
[58,59], but data are controversial. It is not clear whether children who participate in weight loss programs have pathological sensory thresholds and whether these changes are normalized after treatment.

In obese children, hyperactivity of the limbic and paralimbic brain areas was observed during presentation of food stimuli in the hungry state. These areas remain activated after a meal and after the presentation of food stimuli
[60]. It is not clear whether and how processing of food stimuli plays a role in weight loss treatment.

When subjects were asked to fill the same amount of water in a low, wide glass and in a tall, narrow one tend to fill more water in the low, wide glasses due to an optical illusion
[61,62]. This implies that the estimation of food portion sizes may be affected by their visual appearance
[61,62]. It is not known whether the number of correct/incorrect estimates of quantities of food and liquids is different in our study population and whether this has an impact on prediction of weight loss and weight maintenance.

An indirect measurement of eating behavior is the eating rate (run of a spoon or a fork to the mouth per time unit)
[63]. Moreover, an increased eating rate may be associated with excess weight
[64]. It was shown
[65] that the movement of eating is different to other accidental or deliberate motor activities of the dominant hand or arm. On this basis, a device was developed called "bite-counter"
[66] which can measure the eating rate. The bite-counter had not been evaluated in children and adolescents.

While the list of potential measurements within and across these clusters is virtually unlimited, their selection can be determined based on two criteria: a) feasibility in a pediatric inpatient setting at the beginning and the ending of a therapy within a limited time frame, and b) having been shown previously to bear relevance in (childhood and adolescent) obesity.

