#### Cluster 4: Eating behavior

For psychological assessment of eating behavior the inventory of eating and weight problems for children (EWI-C)
[78] will be used, in addition, also a specific questionnaire asking for their food preferences and regular eating behaviors at home.

To validate eating behavior as indicated in the questionnaire, children will be allowed a 20-minute post-stress recovery (see above) while watching a movie on TV and taking snacks of different caloric density ad libitum, with the experimenter not present during that time. However, unbeknown to the children the snack plate will be filmed during this period. In addition, food will be weighted before and after the session and consumed calories will be calculated. In addition, some of the children will carry a novel "bite-counter" (Bite Technologies, Pendleton, South Carolina, USA)
[66,101] that registers the numbers of arm and hand movements typical for eating behavior. Video-recordings will be used to validate the bite counting technology, as well.

Furthermore, the cognitive ability to discriminate volumes of food and liquids will be tested. Therefore, pairs of glasses (e.g. low, wide glass versus a slim, tall glass), of plates and bowls with pre-defined amounts of water or uncooked lentils (representing food) will be presented. The children and adolescents will be asked to estimate the quantities of the provided amounts. They will also be asked to estimate the amount of food needed to satisfy normal hunger.

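### Skin-conductance electrodes are placed on the dominant hand, and the Cluster 4 text, unlike Table 1, has the child eating with that hand during the post-stress recording

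*Protocol article*

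**What the plan says.** Four places in the protocol article bear on this point.

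- **Cluster 3: Autonomic regulation.** On electrode site: "Skin conductance will be measured parallel to ECG and EGG by using two separate finger electrodes on the dominant hand". On the recording windows: "An electrocardiogram (ECG) will be recorded for off-line analysis of heart-rate variability (HRV) during rest (20 min) and following a mental stress test". The post-stress period is also given as 20 minutes. EGG is recorded at the same time, and again for 20 minutes after the water load.
- **Cluster 4: Eating behavior.** On snack timing: "children will be allowed a 20-minute post-stress recovery (see above) while watching a movie on TV and taking snacks of different caloric density ad libitum". The experimenter is out of the room during this time. Some of the children also carry a bite counter, which "registers the numbers of arm and hand movements typical for eating behavior".
- **Psychophysiological investigations, Table 1, second session.** The order is baseline recording, stress test, post-stress period, water load, post-water-load period, and then a separate 20-minute row, "Eating behavior test with snacks". Skin conductance is named in one row only, "ECG/EGG/SCL Baseline".
- **Subjective and objective measures of eating behavior (background).** The rationale for the bite counter is that "the movement of eating is different to other accidental or deliberate motor activities of the dominant hand or arm".

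The Statistics section names the ECG/IBI stress response as the Cluster 3 key variable and caloric intake per time unit as the Cluster 4 key variable.

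**The concern.** Read together, the Cluster 3 and Cluster 4 sections wire the fingers of the hand that the protocol itself links to eating, and then let the child eat freely during the recording. Two measurements are at stake.

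The first is skin conductance. Gripping and lifting food can disturb finger electrodes, and nothing comparable happens in the resting baseline. A disturbance that grows with eating would link a Cluster 3 measure to Cluster 4 intake for reasons unrelated to autonomic function.

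The second, and more important, is the eating measure. Wired dominant fingers may slow the child or make the child use the other hand. That would affect caloric intake per time unit and, in the children who carry the device, the comparison of bite counts with video.

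Behind both lies a conflict within the article: the text and Table 1 disagree on when the snacks are given.

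**Working it through.** **The plan's own figure.** The only computed design figure is the sample size. With four key variables and all correlations at 0.3:

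- R² = 4 × 0.3² / (1 + 3 × 0.3) = 0.36 / 1.9 = 0.189
- f² = 0.189 / (1 − 0.189), which is 0.234 before rounding of R²
- The smallest N with power of at least 0.80 at alpha 0.05 is 57 (power 0.809).

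The stated 57 is reproduced and does not depend on the present point. It does confirm that the calculation uses one key variable per cluster. Caloric intake per time unit is therefore one of the four predictors behind it, and skin conductance is not.

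**Does eating overlap recording?** Inputs are the second-session durations in Table 1, in minutes:

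| Row | Low | High |
|---|---|---|
| Welcome | 5 | 10 |
| Media questionnaire | 5 | 10 |
| Interoception test | 5 | 5 |
| Baseline recording | 20 | 20 |
| Stress test | 5 | 5 |
| Post-stress period | 20 | 20 |
| Water load | 2 | 5 |
| Post-water-load period | 20 | 20 |
| Snack test | 20 | 20 |
| Stress and coping questionnaire | 15 | 20 |
| **Total** | **117** | **135** |

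*On Table 1:*

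- Post-stress start: 5 + 5 + 5 + 20 + 5 = 40 (low); 10 + 10 + 5 + 20 + 5 = 50 (high).
- Post-stress end: 60 to 70 minutes.
- Snack start: 60 + 2 + 20 = 82 (low); 70 + 5 + 20 = 95 (high).
- Overlap of snacks with post-stress recording: 0 of 20 minutes.

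*On the Cluster 4 text:* the back-reference attached to the post-stress recovery can only sensibly point to the 20-minute post-stress period under Cluster 3. Overlap: 20 of 20 minutes.

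**Can the session length decide between the two?** Merging snacks into the post-stress period removes 20 minutes, giving 97 to 115.

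| Session length | Separate snack block (117–135) | Merged (97–115) |
|---|---|---|
| 14:00–16:00, text (120 min) | fits only at the low end | fits |
| 14:30–17:00, Table 1 (150 min) | fits | fits |

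The text's session length suits the merged reading and Table 1's suits either, so the timing does not settle the matter.

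**Water load.** The text describes an EGG recording after drinking. It does not state that any signal is recorded during drinking, so no exposure is counted there.

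**Route into the analysis.** Step 1 of the Statistics section screens variables within each cluster, and step 2 takes the most sensitive one per cluster. Skin conductance can reach the regression only by being selected in this way.

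**The case against.** A reader might infer that the electrodes are certainly worn while the child eats and drinks, so that the signal is corrupted and eating is impeded. The documents do not support that. Table 1 puts snacks after all the recording blocks and names skin conductance only at baseline. The text has recording after the water is drunk, not during it. Nothing in the article describes movement artefact, impaired eating or removal and refitting of electrodes, and it gives no figure for any of these. Whether the electrodes come off before the snack test is also a detail that an article may leave to the full protocol. All of this stands, and it makes the point conditional.

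Three further objections stand in part.

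- Skin conductance is neither a primary or secondary outcome nor a key variable. That is correct and limits the harm on that side, but caloric intake per time unit is a key variable.
- Changing the hand does not make the post-stress window comparable with baseline if the child is eating in it. Eating would also affect ECG/IBI and EGG, whichever hand is wired. This is right, and it is why the timing must be settled too.
- Asking a child to keep one hand still constrains a free snack test, and with the experimenter absent the request could not be enforced. This is a real but small cost, and it disappears if the electrodes are off during the snack test.

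What none of these removes is that the article states the dominant hand outright and gives two incompatible times for the snacks, one of which falls wholly inside a recording window.

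**Conclusion.** The point holds conditionally and is of modest size. The placement on the dominant hand and the conflict over snack timing are both plain on the page. If the Cluster 4 text governs, all 20 post-stress minutes are exposed at admission and at discharge, in every child who eats with the dominant hand. If Table 1 governs, the snack exposure is zero. These minutes measure possible exposure, not bias; the size of any artefact or hindrance cannot be derived from the documents.

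The main measure at risk is caloric intake per time unit, followed by the bite-counter validation in some children. Post-stress skin conductance is at risk only as a step 1 candidate. Measurement of the primary outcome, change in BMI-SDS, is not touched.

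The conclusion rests on two assumptions: that the post-stress recovery in the Cluster 4 section is the recording period of the Cluster 3 section, and that children eat mainly with the dominant hand, as the background section implies. That finger movement can disturb the signal, and that wired fingers can hinder eating, is general measurement reasoning and not a finding in the documents.

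**What to change.** Make two changes together.

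1. In the Cluster 3 section, specify the non-dominant hand for the skin-conductance electrodes, for every child and at both the admission and the discharge assessment. This keeps the eating hand free under either schedule.
2. Reconcile the Cluster 4 section with Table 1 so that snacking does not fall inside the post-stress ECG, EGG and skin-conductance recording, and state that the finger electrodes are off during the snack test. This also protects the ECG/IBI stress response, the Cluster 3 key variable, which a change of hand alone would not do. The two session lengths, 120 and 150 minutes, should be aligned at the same time, because a separate snack block needs 117 to 135 minutes.

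The cost is a short edit to the text and the measurement instructions. If the electrodes nevertheless stay on while the child eats, some constraint on one hand remains.
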